### 500 **13.3. Visit 1 and 3 (week 0 and week 24)**

501 The participants underwent an FDG-PET at the beginning and end of the study.

502 FDG-PET studies were performed using a Siemens Biograph TruePoint PET-CT  
503 scanner, which integrated a state-of-the-art detector with lutetium  
504 oxyorthosilicate crystals. Patients fasted for at least 6 hours prior to the scan. The  
505 dose was administered 30 minutes before image acquisition. Current European  
506 recommendations for the acquisition of FDG-PET brain studies were followed  
507 (Varrone et al. 2009).

508 FDG-PET images were pre-processed using the Statistical Parametric Mapping 12  
509 program (Wellcome Trust Centre for Neuroimaging, Institute of Neurology,  
510 London). The analysis of cerebral metabolism was carried out using a broad region  
511 of interest that included much of the left hemisphere. This region of interest was  
512 obtained by comparing, through voxel-based analysis, a cohort of 70 PPA patients  
513 evaluated at two time points, and it was the region of interest used for sample size  
514 calculation. The relative uptake in this area was calculated at baseline and after 6  
515 months of the study.

## 516 **14. EFFICACY OUTCOMES**

- 517 **● Primary outcome**

518 The primary variable of the study for the assessment of efficacy is the change in  
519 regional cerebral metabolism between the baseline and final visits.

520       • **Secondary outcomes**

521 MLSE

522 Trained Word Naming

523 Spontaneous Speech: number of words per minute

524 Activities of Daily Living: IDDD

525 Neuropsychiatric Symptoms: NPI

526 Adverse events related to treatments during the 6 months following  
527 randomization.

528 **15. SAFETY MEASURES AND RISK MANAGEMENT**

529 It is the responsibility of the investigator to detect and document any event that  
530 meets the criteria and definitions of an adverse event or serious adverse event as  
531 established in this protocol. Safety assessments will be conducted in accordance  
532 with Good Clinical Practice guidelines and current legislation. Adverse effects will  
533 be recorded during each study visit. The analysis will include the type of adverse  
534 effect and its frequency.

535 **15.1. Definitions**

536 **15.1.1. Adverse Event (AE)**

537 Any harmful health incident in a patient or clinical trial subject treated with a  
538 medication, regardless of whether there is a causal relationship with the  
539 treatment. An AE can therefore be any unfavorable and unintended sign (including  
540 an abnormal laboratory finding), symptom, or disease temporally associated with  
541 the use of an investigational drug, whether or not it is related to the drug.

542 **15.1.2. Adverse Reaction (AR)**

543 Any harmful and unintended reaction to an investigational drug, regardless of the  
544 dose administered. In this case, there is a suspected causal relationship between  
545 the investigational drug and the adverse event.

546 **15.1.3. Serious Adverse Event (SAE) and Serious Adverse Reaction (SAR)**

547 Any adverse event or adverse reaction that, at any dose: results in death, is life-  
548 threatening, requires hospitalization or prolongs an existing hospitalization,

causes permanent or significant disability or incapacity, or leads to a congenital anomaly or birth defect. For reporting purposes, any suspected AE or AR considered medically significant will also be treated as serious, even if it does not meet the above criteria. This includes medically significant events requiring intervention to prevent one of the outcomes. Additionally, any suspected transmission of an infectious agent through a medication will be reported as serious.

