|                      |                                   |           |                                           |    |         |        |                                                                                           |
|----------------------|-----------------------------------|-----------|-------------------------------------------|----|---------|--------|-------------------------------------------------------------------------------------------|
|                      |                                   |           |                                           |    |         |        | depending on initial deficit severity.                                                    |
| Tsapkini et al. 2018 | 14 nfvPPA
12 lvPPA
10 svPPA | Crossover | tDCS left inferior frontal gyrus vs. sham | 15 | 3 weeks | USA    | tDCS improvement in in naming/spelling, particularly in nfvPPA and lvPPA compared to sham |
| Roncero et al. 2019  | 12 PPA                            | Crossover | tDCS P3, F3, or sham                      | 10 | 2 weeks | Canada | Improvement in naming, especially for trained items.                                      |

88

89 In a previous study, our group treated 20 patients with PPA (non-fluent and  
90 semantic variants) through 15 sessions of high-frequency repetitive TMS,  
91 observing clinical improvement in various linguistic tasks, a reduction in apathy,  
92 and an increase in cerebral metabolism in several brain regions primarily  
93 associated with language networks and the default mode network (Pytel et al.,  
94 2021). The TMS treatment protocol was selected based on a prior phase in which  
95 different protocols were tested (excitatory vs. inhibitory protocols, targeting  
96 different brain areas). It was concluded that excitatory protocols produced a more  
97 favorable effect, and different brain areas were selected as the most suitable (e.g.,  
98 left inferior frontal gyrus, dorsolateral prefrontal cortex, etc.).

99

| Table 2. TMS Studies in PPA (Excluding Studies with 5 or Fewer Patients) |              |        |                 |          |          |         |          |
|--------------------------------------------------------------------------|--------------|--------|-----------------|----------|----------|---------|----------|
|                                                                          | Participants | Design | Neuromodulation | Sessions | Duration | Country | Findings |

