### **7.1. TMS INTERVENTION**

All patients included in the study will receive TMS and speech therapy.

- TMS: TMS is a technique for electrical stimulation of brain tissue through the generation of a magnetic field, modulating neuronal activity at the

stimulation site and interconnected neural networks. The study will use transcranial magnetic stimulation (TMS) delivered with a figure-of-eight coil guided by neuronavigation. An intermittent theta-burst stimulation (iTBS) protocol will be applied, following current clinical practice guidelines and recommendations for TMS (Lefaucheur et al., 2020). The theta-burst protocol allows for shorter stimulation times (<10 minutes per session) with effects comparable to traditional repetitive stimulation protocols. Neuronavigation, based on the patient's own MRI, ensures accurate targeting of the stimulation area, reducing inter- and intra-individual variability. Treatment will be applied to the left dorsolateral prefrontal cortex. Each patient will receive 10 consecutive sessions during the first 2 weeks, followed by 1 weekly session until completing 6 months of treatment.

- Sham TMS: For the sham TMS group, a sham coil indistinguishable from the therapeutic coil will be used. Sessions will occur at the same frequency as the active TMS group, ensuring that patients remain unaware of whether they are receiving sham or standard TMS. Only the staff responsible for administering the TMS will know the treatment assignment.
- Blinding: The evaluator conducting follow-up assessments will be blinded to the treatment allocation (active or sham TMS). Only the technician applying the TMS will know whether the treatment is active or sham.
- If a patient misses a scheduled TMS or speech therapy session, it will be rescheduled, preferably within the same week. If the treatment cannot be performed that week, the missed sessions will be scheduled for the following weeks (with one additional session per week). The maximum period without treatment sessions will be 4 weeks. If this period is exceeded, the patient will be withdrawn from the study.

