## **12. DATA COLLECTION AND MONITORING**

### **I. Baseline Visit**

At the Cognitive Neurology Clinic of Hospital Clínico San Carlos, patients who meet the eligibility criteria will receive both verbal and written information about the study. They will have the opportunity to ask any questions, as well as consult with their family and/or friends regarding their decision to participate.

If the patient decides to participate, two copies of the informed consent form will be signed—one will be given to the patient, and the other will be filed in the investigator's study archive. Participation in the study will also be documented in the patient's medical record, including the date of inclusion, the version of the signed consent form, and confirmation that a copy was provided to the patient.

The patient will be assigned a unique study code and randomized via the eCRF system.

380 During the Baseline Visit, the following activities will be performed:

- 381 ✓ Evaluation of inclusion and exclusion criteria.
- 382 ✓ Delivery of the patient information sheet and informed consent form.
- 383 ✓ Randomization.
- 384 ✓ Clinical Information: Date of birth, sex, years of formal education, year of
- 385 PPA diagnosis, and relevant medical history.
- 386 ✓ Concomitant Medication: Details of current medications.

387 The patient will be provided with a patient diary to record adverse events, visits to  
388 other specialists, and/or any required healthcare services. This diary is intended to  
389 assist the patient in adhering to treatment routines and facilitate study  
390 participation. The information recorded in the diary will be verified by a member of  
391 the research team and documented in the patient's medical records and eCRF  
392 during study visits.

393 After this visit, treatment appointments will be scheduled to ensure compliance  
394 with the established timeframes. The treatment initiation (corresponding to the  
395 relevant phase) must occur within 30 days following Visit 1 (Baseline Visit).

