## 414 **III. Intermediate Visit (+3 months after the start of the intervention)**

415 During this visit, the patient will be evaluated following this schedule of activities:

- 416 ✓ MLSE
- 417 ✓ Trained Word Naming
- 418 ✓ Spontaneous Speech (Words per Minute)
- 419 ✓ IDDD
- 420 ✓ NPI
- 421 ✓ Patient Diary Review
- 422 ✓ Concomitant Medication Review

423

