### 439 **13. ASSESSMENTS**

#### 440 **13.1. Baseline Visit**

- 441 - Age
- 442 - Sex
- 443 - Years of formal education
- 444 - Languages spoken and age of acquisition
- 445 - Mother tongue
- 446 - Laterality
- 447 - Family history of neurodegenerative diseases

448 - Duration of symptom

449 - Language assessment: Different tasks that assess language domains: Cookie  
450 Theft picture; Paradis narrative sequence picture; reading narrative text, words,  
451 capitalized words, foreign words, and non-words; omission of initial phoneme;  
452 spelling words; repetition of words, non-words, syllables and sentences; semantic  
453 association; naming pictures and actions; word-picture matching; synonyms;  
454 picture-action matching; orophonatory praxis; verb tense agreement; sentence  
455 comprehension.

456 - Cognitive assessment: Test included in NEURONORMA protocol (Peña-  
457 Casanova et al., 2009): memory span (forward and backward digit spans), the  
458 Corsi block-tapping test, Trail Making Test (TMT), Symbol Digit Modalities Test  
459 (SDMT), Visual Object and Space Perception Battery (VOSP; subtests for object  
460 decision, progressive silhouettes, position discrimination, and number location),  
461 Judgement of Line Orientation (JLO), Tower of London-Drexel University, Rey-  
462 Osterrieth Complex Figure Test (copy and memory), and Stroop Color-Word  
463 Interference Test.

464 - Addenbrooke's cognitive examination III (ACE-III): ACE-III is a general cognitive  
465 screening tool that assesses attention (temporal spatial orientation, 3-item  
466 registration, serial subtractions) memory (recall of 3 items, anterograde memory  
467 of a name and address, retrograde memory, and recall and recognition of a name  
468 and address) verbal fluency (words beginning with "p" and animals), language  
469 (comprehension of a complex command, sentence writing, single word repetition,  
470 proverb repetition, a 10-item confrontation naming task, a semantic task, and  
471 reading) and visuospatial skills (copy of intersecting infinity loops, copy of a cube,  
472 drawing of a clock, counting dots, and identifying incomplete letters).

473 **13.2. Visit 1, 2 and 3 (week 0, week 12 and week 24)**

474 - Mini-Linguistic state examination (MLSE)

475 The MLSE is a brief screening tool designed to assess language impairments in  
476 various neurodegenerative disorders, particularly in PPA. It includes a series of  

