#### 592 **15.5. Procedure for AE Recording**

593 The recording of AEs must be carried out by the study's investigative team. The  
594 investigator will systematically monitor and document all reported adverse events  
595 in the clinical records, whether spontaneously reported by the patient or identified  
596 during study visits. This monitoring will occur from randomization until the final  
597 follow-up visit for each subject.

598 Only ARs and all SAEs/SARs will be recorded in the CRF for each subject. For these  
599 events, the investigator must specify the start date, causality, intensity, severity,  
600 treatment, and outcome. If treatment is administered for any of these events, it  
601 must also be recorded in the CRF.

602 All AEs will be followed until resolution, stabilization, or determination that the  
603 investigational treatment or participation in the study was not the cause. Likewise,  
604 follow-up will be conducted for any AEs persisting after the study has concluded  
605 until their final outcome is determined.

606 Analytical abnormalities or other evaluations (e.g., vital signs) detected during the  
607 trial, or present at the time of signing the informed consent and worsening after  
608 the trial begins, will only be recorded as specified in this protocol if they are  
609 considered clinically significant by the investigator or related to the investigational  
610 medication.

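### After treatment starts, adverse events and medication changes have a scheduled enquiry only at months 3 and 6, so about 20 of 32 to 34 TMS sessions pass before the first one

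*Protocol*

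**What the plan says.** On when events are recorded, Section 15 (Safety measures and risk management) says adverse effects will "be recorded during each study visit. The analysis will include the type of adverse" effect and its frequency.

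On how they are found, Section 15.5 has the investigator document events "in the clinical records, whether spontaneously reported by the patient or identified" at study visits, from randomization to the last follow-up visit.

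On the visits themselves, Section 13.2 gives "Visit 1, 2 and 3 (week 0, week 12 and week 24". Section 12 lists Visit 1 before the intervention, then the "Intermediate Visit (+3 months after the start of the intervention" and a final visit at 6 months. After treatment starts, diary review and concomitant medication review appear only in the lists for those last two visits.

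On the time between visits, Section 12 (Baseline Visit) says: "The patient will be provided with a patient diary to record adverse events, visits to" other specialists and other care. The research team verifies the diary at study visits.

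On treatment, Section 7.1 says: "Each patient will receive 10 consecutive sessions during the first 2 weeks, followed by 1 weekly session until completing 6 months of treatment". Section 7.2 gives 4 speech therapy sessions in the first 2 weeks and one a week after that, each directly after TMS. Neither section assigns a question about adverse events or medication to any session. On blinding, Section 7.1 says: "Only the technician applying the TMS will know whether the treatment is active or sham".

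Section 14 lists treatment-related adverse events over 6 months among the secondary outcomes.

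**The concern.** The weakest period of enquiry coincides with the most intensive period of stimulation. Until month 3, a symptom reaches the record only if the patient raises it or writes it down. Section 5.2 requires language to be the patient's main deficit, so both routes lean on the impaired function. Caregivers already supply the IDDD and the NPI (Section 13.2) but are given no part in reporting adverse events.

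An outcome of the trial is at stake. Section 15.5 requires a start date and a causality judgment for each event entered in the CRF, and Section 15.2 rests causality largely on timing. An event from the first two weeks that is first discussed at month 3 may be missed or badly dated.

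There is also a blinding aspect. Whatever a patient mentions at a TMS session is heard first by the technician, the one person who knows the arm, and no wording is fixed for what is asked or passed on.

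**Working it through.** The protocol gives no count of sessions before the first enquiry, so there is no stated figure to reproduce. The count follows from the schedule.

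**Inputs.** TMS: 10 sessions in weeks 1 and 2, then 1 a week (Section 7.1). Speech therapy: 4 sessions in weeks 1 and 2, then 1 a week (Section 7.2). Visits: weeks 0, 12 and 24 (Section 13.2), described in Section 12 as 3 and 6 months after the start. Three months may also be read as 13 weeks and six months as 26.

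**Formulas**, for week w of 2 or more: TMS sessions = 10 + (w − 2); speech therapy sessions = 4 + (w − 2).

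| Week | TMS sessions | Speech therapy sessions |
|---|---|---|
| 2 | 10 | 4 |
| 12 | 20 | 14 |
| 13 | 21 | 15 |
| 24 | 32 | 26 |
| 26 | 34 | 28 |

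**Results.**
- Share of TMS sessions before the first scheduled enquiry: 20/32 = 0.625, or 21/34 = 0.618; about 62% either way.
- Time from the end of the intensive block to that enquiry: 12 − 2 = 10 weeks (11 on the 13-week reading).
- Sessions between the two on-treatment visits: 32 − 20 = 12, or 34 − 21 = 13.
- Speech therapy contacts before the month-3 visit: 14 or 15, of which 4 fall in the intensive block. None carries a scheduled safety question at present.

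**Reading the sections together.** Section 15 ties recording to study visits. Section 12 sets out what happens at each visit and calls the treatment contacts appointments or sessions. Section 15.5 names spontaneous report and study visits as the two routes, and the diary is opened by staff only at visits. The month-3 and month-6 lists contain diary review but no separate adverse-event question; active recording there comes from Section 15.

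**The case against.** The strongest reply is that patients are seen in person at every session. Section 15 makes the investigator responsible for detecting events, Section 15.5 speaks of systematic monitoring from randomization onwards, and nothing says that a session cannot be an occasion for it. Part of this stands. The gap is in scheduled enquiry, not in contact, and the word only depends on reading study visits as those in Sections 12 and 13. That is the natural reading, but the protocol does not spell it out.

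The diary also counts. It is kept during treatment, so it would be wrong to say that early events must be recalled from memory at week 12. It is still completed by the patient and checked only at visits. The eligibility rules count too: CDR is 1 or less, and mutism or severity that prevents participation is excluded. Patients can report something; the documents do not show how well. The 24-hour rule for serious events runs from awareness, so it does not itself detect anything.

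Three stronger readings are tempting and are not supported.
- **That the safety comparison is biased towards no difference.** If both arms lose the same fraction of events, the absolute difference shrinks but the ratio does not. If capture differs by arm, the error can go either way. The documents give neither event rates nor capture rates.
- **That an added drug which lowers the seizure threshold would go unnoticed with consequences.** Section 5.3, item 13e allows such additions, Section 8 declares no medication incompatible, and no action is attached to them. What remains is an incomplete medication record.
- **That exposure exceeds all earlier experience and safety is therefore in doubt.** The group's earlier study treated patients with non-fluent and "semantic variants) through 15 sessions of high-frequency repetitive TMS", and 20 sessions is more than 15. But Section 2's remark that long-term effects are unstudied is limited to the authors' knowledge and concerns benefit.

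**Conclusion.** The point holds as a weakness in ascertainment. Following the protocol as written, the full 10-session block and about 20 of 32 sessions (21 of 34) precede the first scheduled question about adverse events or medication, in patients whose main deficit is language and for an outcome that the trial intends to report. Incomplete and poorly dated events are the likely consequence. How many would be lost, and whether the loss differs between arms, cannot be worked out from the documents.

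The conclusion assumes that treatment sessions are not study visits and that sessions run to schedule. If the sponsor already intends enquiry at sessions, the protocol needs to say so. This is content for the protocol and not something to leave to an SAP. It is a cheap improvement, not a flaw that invalidates the design.

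**What to change.** In Sections 15.5 and 7.2, add a short question set in fixed wording on new symptoms and on new or changed medication since the last enquiry. The speech therapist, who is not unblinded under Section 7.1, asks it at every speech therapy session and notes the dates. That gives 4 enquiries in the first two weeks and 14 by week 12, without routing them through the technician.

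State that the investigator reviews the answers. Section 15.5 at present admits only adverse reactions and serious events to the CRF, so amend that rule to let the answers be entered. State also that a caregiver may help to complete the diary and may answer when present; attendance need not be required. No rule on withholding or changing treatment is needed for this purpose, and none should be added.

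The cost is one extra form, a minute or two at sessions already scheduled, and more low-grade events reported. No new staff or visits are needed. If the therapist also carries out follow-up assessments, which the protocol does not say, symptom reports could hint at the arm, and the roles should then be kept apart.

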#### **15.1.4. Unexpected Adverse Reaction (UAR):**

Any AR whose nature, intensity, or consequences do not align with the reference information for the medication (e.g., the investigator's brochure for an investigational drug not yet authorized for marketing, or the product's data sheet in the case of an authorized medication).

#### **15.2. Causality Assessment Criteria**

The causal relationship between the investigational product and the occurrence of an AE will be established based on clinical judgment. Other potential causes, such as the natural history of underlying diseases, concomitant treatments, other risk factors, and the temporal relationship of the event to the investigational product, will be considered and evaluated.

The causality of an AE with the investigational medication will be determined based on the following definitions:

- **Related AE:** The temporal relationship of the AE with the investigational product suggests a possible causal relationship, and the event cannot be explained by factors such as the patient's clinical condition or therapeutic interventions.
- **Unrelated AE:** The temporal relationship of the AE with the investigational product suggests an improbable causal relationship, or other factors (such as concomitant medications, conditions, or other therapeutic interventions) provide a satisfactory explanation for the AE.

The investigator must assess the causality of all adverse events (serious or not) and report this assessment in accordance with the requirements for reporting serious adverse events, if applicable.

If the investigator is uncertain about the causality, for reporting purposes, the adverse event will be considered related to the investigational product.

